### Evaluation procedure

2.6

(1)Evaluation 1 (baseline), first day of cardiorespiratory rehabilitation(2)Evaluation 2 at approximately 4.5 weeks of cardiorespiratory rehabilitation (Intermediary)(3)Evaluation 3 at approximately week 9 of cardiorespiratory rehabilitation (final)(4)Evaluation 4 follow-up, 2 months following ending of cardiorespiratory rehabilitation.

Data will be stored on the researchers’ computers and in the cloud with shared access among researchers involved in the trial. The evaluation and evolution sheets will be archived within the Laboratory of Sensory-Motor Rehabilitation Engineering, in addition to the digital copy, also stored in the cloud.

### Intervention

2.7

#### Schedule

2.7.1

Procedures will be performed twice a week on alternate days for 9 weeks, totaling 18 sessions of therapy, with each session lasting approximately 1 hour.

Patients will be allowed to access the researchers by telephone and email in case of any questions regarding the project or any symptoms.

#### Cardiorespiratory rehabilitation and photobiomodulation procedures

2.7.2

The treatment session will be divided into following 5 steps:

(1)Step 1: Initial seated rest before exercise, vital signs, and PBM Therapy.

Seated rest before exercise period should be 10 minutes. Concurrent with seated rest, vital signs should be measured followed by the PBM procedure.

Vital signs data such as systemic blood pressure, heart rate, respiratory rate, peripheral oxygen saturation, and BORG will be measured.

Group CCR will rest (seated) without PBM or placebo PBM.

Group CR-PBM will receive transcranial PBM Therapy (wavelength 810 nm laser, beam area on the skin 0.028 cm^2^, laser power 100 mW, irradiance 3.5 W/cm^2^, treatment time 30 seconds per point, energy 3 J per point, and fluence of 107.1 J/cm^2^ (Irradia, Stockholm, Sweden). The location of PBM Therapy will be in the middle cerebral arteries and the anterior cerebral artery (electroencephalogram points F7, F8, and AFz) according to the International 10–20 System of the electroencephalogram.

Group CR-PlaceboPBM will receive PBM Therapy with the device inactive. The therapist will be blinded to active or placebo mode.

After initial seated rest, vital signs data (systemic blood pressure, heart rate, respiratory rate, peripheral oxygen saturation, and BORG) will be repeated.

(2)Step 2: Aerobic training phase: (i) Warm-up, (ii) Aerobic resistance training, and (iii) Cool down.

These phases will occur on a treadmill (Moviment RT200, São Paulo, Brazil), using support of the BrainMov Rehabilitation and Physical Activity Station (Fig. 2). This is composed of 4 iron pillars, where extensors and elastic cords are added, favoring suspension and stabilization of people with mild to severe impairment of neuromuscular function. This structure allows users to practice dynamic exercises that could not be performed without the help of others. The equipment is safe and thus adapted for rehabilitation and training of people with reduced mobility, providing aerobic training and muscle strengthening.^[25]^

(i)Warm-up: 5 minutes of aerobic heating. The patient will walk at low speed on the treadmill for 5 minutes. Systemic arterial pressure, heart rate, and peripheral oxygen saturation will then be assessed.(ii)Aerobic resistance training: The individual will walk on the treadmill for 15 minutes, at an intensity according to the patients training heart rate. This will be determined by the Karvonen equation [Training heart rate = % of desired effort x (predicted maximum heart rate - resting heart rate) + resting heart rate], where predicted maximum heart rate is 220-age. The percentage of effort that will be considered in the THR equation will be between 50% and 70%.^[26]^ Monitoring will also be guided via the effort perception BORG scale, maintaining a moderate subjective perception effort (12--14 of BORG scale). At 7 and 15 minutes, systemic blood pressure, heart rate, and peripheral oxygen saturation will again be assessed.^[26]^(iii)Cool down: 5 minutes. Treadmill speed will be decreased gradually to prevent falling injury. Where patients are walking at the minimum treadmill speed, during aerobic resistance, cool down will occur with the treadmill off, in an upright position. Systemic blood pressure, heart rate, and peripheral oxygen saturation will again be assessed.

**Figure 2 F2:**
[figure not shown]
Rehabilitation station and physical activity BrainMov.

After aerobic training, patients will rest (seated) for 5 minutes, following which blood pressure, heart rate, and peripheral oxygen saturation will again be assessed.

(3)Step 3: Respiratory exercises and muscle strengthening phase

Two breathing exercises and 2 muscle strengthening exercises will be performed as follows:

Breathing exercises:

(i)Exercise of diaphragmatic breathing: To promote pulmonary expansion and strengthen of respiratory muscles, the patient will be instructed to breathe in the diaphragmatic pattern, where in the inspiratory phase, the air must be inspired by the nostrils, contracting the diaphragm, so that the abdominal and thoracic region spreads (mainly the abdomen). In the expiratory phase, the air must be exhaled by the mouth, associated with abdominal contraction. This will be performed in a sitting position. Patients will perform 3 sets of 8 repetitions.(ii)Fractionally inspiratory breathing exercise: In the seated position, patients will be instructed to perform 3 brief and consecutive inspirations, in order to achieve total lung capacity. After a short inspiratory pause, the individual will be instructed to release all the air through the mouth (exhalation) slowly, smoothly, and with half-closed lips. Patients will perform 3 sets of 5 repetitions.

Muscle strengthening exercises:

(i)Exercise of muscular strengthening in closed kinetic chain of hamstrings, femoral quadriceps, gluteus maximus, and gluteus maximus: Crouching movement, holding in the back, and aided by the Rehabilitation and Physical Activity Station BrainMov. Patients will perform 3 sets of 10 repetitions.(ii)Exercise of muscle strengthening in the open kinetic chain of the iliopsoas and quadriceps femoris groups: Hip and knee flexion movement, facilitating movement of triple flexion during gait. Patients will be able to hold the movement to the back and will be assisted by the BrainMov Rehabilitation and Physical Activity Station to perform the exercise. Patients will perform 3 sets of 10 repetitions.

(4)Step 4: Relaxation phase 5 minutes: Global stretches will be performed for upper limbs and lower limbs, actively associated with slow and gentle breathing.(5)Step 5: Cardiorespiratory rehabilitation and activities of daily life guidelines: In this stage, the patients participating in the trial and their families will be provided with guidelines to facilitate daily life activities and elucidation about the cardiorespiratory rehabilitation process.

Finally, systemic blood pressure, heart rate, and peripheral oxygen saturation will again be assessed.

#### Safety measures

2.7.3

During PBM Therapy, patient, therapist, and any observers will wear safety laser goggles with suitable optical density for the wavelength and intensity used.

For hygiene, the laser probe tip will be cleaned up between patient applications. Vital signs and effort perception (by the scale BORG and training heart rate by the Karvonen equation) will be monitored throughout, in order to identify any changes outside normal physiological ranges. If the peripheral oxygen saturation decrease is equal to or less than 88%, the patient will be supplemented with oxygen, adjusted as necessary. An oxygen gas cylinder, nasal catheter and mask, and ready-to-use air humidification system will be available at the site.

To reduce the minimum risk of falls, in the case of dizziness, abrupt changes in vital signs, or motor function, there will always be 2 physiotherapists close to the patient to support. The treadmill will be immediately disconnected by one of the therapists, and as a preventive measure, patients will use the BrainMov Rehabilitation and Physical Activity Station equipment to maintain greater stability and suspension if they lose their balance.

Patients may discontinue treatment at any time if they feel sick or feel any discomfort.

Should a patient present worsening of any symptom caused by the therapy, it will be immediately interrupted, and if necessary, the patient will be rescued.

### Outcome measures

2.8

(1)Muscle electrical activity (surface electromyograph, 830 Wi-fi, EMG System do Brasil, Brazil): Surface electrodes will be positioned on the rectus femoris and biceps femoris muscles, during the squatting movement: 10 seconds of signal collection (in triplicate);(2)Bipodal balance during the squat movement: EMG balance evaluation will be performed during the squat movement in the force platform (stabilometric analysis in kgf), 10 seconds of signal collection (in triplicate);(3)Pulmonary function (Cosmed MicroQuark Spirometer, Brazil): Using the spirometry technique, forced expiratory volume in the first second; Tiffeneau index and maximal voluntary ventilation will be evaluated by respiratory maneuvers. Volume of air exhaled in the first second of the forced vital capacity maneuver will be evaluated.(4)Respiratory muscle strength (inspiratory and expiratory): Respiratory muscle strength will be evaluated by the analog manovacuometer, 0 ± 300 cmH_2_O, Ger-Ar;(5)Expiratory peak analysis: force and velocity of airflow from inside the lungs using the Peak Flow Meter, NCS expiratory flow meter.(6)Thoracic-abdominal expansion and mobility: A common metric tape (1.5 m) positioned at the axillary, xiphoid, and abdominal levels will be used, which will measure inspiratory and expiratory mobility values and be subtracted (inspiration - expiration).(7)Blood circulation: Assessed with an infrared thermographic camera (ThermaCam FLIR S65HS, Sweden), blood circulation of the lower limbs will be evaluated by temperature difference;(8)Heart rate variability as an indication of autonomic nervous system responses: assessed by means of a frequency meter (Polar RS800, Finland, California) during treadmill aerobic training for 40 minutes (5 minutes initial seated rest, 30 minutes of exercise, and 5 minutes of final seated rest). R-R intervals will be analyzed;(9)Blood lactate level: measured by a lactometer with lactate reagent tapes (Accutrend PLUS from Roche). Blood samples will be collected before and after treadmill beginning aerobic training;(10)6-minute walk test (Adapted): The 6-minute walk test will be adapted for neurological patients: evaluation of parameters of exercise tolerance on treadmill (Moviment RT200, Brazil) and vital signs responses during and recovery. Patients will be assisted by the BrainMov Rehabilitation and Physical Activity Station to stabilize the trunk and thus stand erect to walk on the treadmill;(11)Quality of life using the Short Form 36: assessing domains of functional capacity, physical appearance, pain, general health, vitality, social aspect, emotional spectrum, and mental health;(12)Cognitive functions: using the Mini-Mental State Examination.

### Statistical analysis

2.9

Data will be stored in Excel (Windows) and in the cloud, organized as mean and standard deviation. Statistical analysis will be carried out within the University of Vale do Paraíba institution. Assumption of normality will be checked, to direct the choice of appropriate statistical test used for intra and intergroup comparisons. Statistical significance will be adopted as *P* < .05. Scientific Data Analysis and Visualization (SciDAVis) will be the software of choice.

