PBM Therapy is considered a noninvasive brain stimulation technique, with potential effects on brain plasticity. Phototherapy has been extensively studied and has been shown to be efficient for a variety of clinical procedures.^[19,20]^

PBM Therapy directly influences the activity of cytochrome c oxidase, an electron transport chain enzyme located on the internal membrane of the mitochondria, responsible for the uptake and absorption of light photons within the red and infrared spectra.^[21,22]^

According to Hennessy and Hamblin,^[23]^ if we want to stimulate the brain, we must radiate the laser light directly to the head, more precisely to the forehead, because there is no hair present, which can dissipate/disperse the photons of light. Radiating laser light directly to the forehead would stimulate the frontal lobes of the cortex, the area responsible for motor function, problem solving, memory, language, initiation, and impulse control.

Clinical studies in humans have demonstrated improvements in a wide range of brain functioning, such as cognitive and memory improvement, improvement of the behavioral picture, such as attenuation of depression and anxiety, and increased cortical oxygenation.^[17,24]^

We believe that the same stimulation of brain tissue, that is, the exposure of nervous tissue to PBM Therapy, could also trigger positive effects peripherally. It is proposed here that cardiorespiratory rehabilitation associated with PBM Therapy may increase performance in physical activity in people with reduced mobility.

Therefore, the aims of this trial will be to evaluate the parameters related to the function of the musculoskeletal and cardiorespiratory system and the impact of PBM Therapy on these parameters, through a rehabilitation and training program for people with reduced mobility.

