### Trial design

2.1

It is a unicentric, randomized, double-blind, placebo-controlled trial with 3 groups: control – only cardiorespiratory rehabilitation (CCR), cardiorespiratory rehabilitation with PBM Therapy (CR-PBM), cardiorespiratory rehabilitation and placebo PBM Therapy (CR-PlaceboPBM). The magnitude of the PBM Therapy effect will be compared statistically across groups. In total, there will be 90 patients (30 in each group). The trial will be conducted at the Clinic School of the University of Paraíba (Brazil), and the sessions will be 1 hour, twice a week for 9 weeks. Baseline, intermediate (4th week), final (9th week), and 2-month follow-up will be performed. Further details on the flowchart of the trial design are shown in Fig. 1.

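### No primary outcome, time point or contrast is named among 12 unranked measures judged at a single unadjusted P < .05

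*Protocol article*

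**What the plan says.** Section 2.8 (Outcome measures) numbers its measures from muscle electrical activity to item 12, "Cognitive functions: using the Mini-Mental State Examination", and labels none of them primary or secondary. Several items hold more than one variable, such as three spirometry indices and eight quality-of-life domains.

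Section 2.1 (Trial design) sets the visits: "Baseline, intermediate (4th week), final (9th week), and 2-month follow-up will be performed". It describes the comparison only in general terms: "The magnitude of the PBM Therapy effect will be compared statistically across groups". There are three arms: rehabilitation alone (CCR), rehabilitation with PBM (CR-PBM) and rehabilitation with placebo PBM (CR-PlaceboPBM). No pair is named as the main one.

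Section 2.9 (Statistical analysis) says that a normality check will serve "to direct the choice of appropriate statistical test used for intra and intergroup comparisons", and then gives the rule: "Statistical significance will be adopted as *P* < .05".

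The Introduction states a directional hypothesis, that "cardiorespiratory rehabilitation associated with PBM Therapy may increase performance in physical activity in people with reduced mobility". No listed measure is tied to it.

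**The concern.** A 5% threshold limits error to 5% for one test. Here it is the only criterion for many tests, and nothing says in advance which result decides whether PBM works. If PBM does nothing, chance alone can readily produce a significant result somewhere in the list, and the plan gives no ground for treating that result as anything less than a PBM effect.

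Within-group tests add a second route to a wrong conclusion. All three arms receive rehabilitation, so improvement within CR-PBM is expected without any PBM effect. A significant change in that arm beside a non-significant change in another could be misread as a difference between arms.

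What is at stake is how far a positive report can be believed. The hypothesis concerns performance in physical activity, yet as written a result on any of the 12 measures could be offered in support of it.

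**Working it through.** **Inputs from the protocol article.** Threshold 0.05 per test (2.9; taken as two-sided, since the text does not say). Outcome measures: 12 (2.8). Post-baseline evaluations: 3 (2.1, 2.6). Arms: 3, with 30 patients each (2.1, 2.4). The article states no familywise error rate, power or effect size, so there is no error or power figure to reproduce. Only the total can be checked: 3 × 30 = 90, which agrees.

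**Inputs assumed.** Correlations between outcomes and between visits. The article gives none, so a range is shown.

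**Step 1. One contrast, one visit, independent outcomes.** P(at least one P < .05) = 1 − 0.95^12 = 1 − 0.540 = 0.460.

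**Step 2. The same 12 tests, correlated.** Each test statistic is modelled as z_j = √ρ·u + √(1 − ρ)·e_j, with u and e_j independent standard normal and no true effect. A test is significant if |z_j| > 1.96. Simulated chance of at least one:

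| Between-outcome correlation ρ | 12 measures | about 25 variables |
|---|---|---|
| 0 | 46% | 72% |
| 0.3 | 40% | 61% |
| 0.5 | 32% | 46% |
| 0.7 | 23% | 32% |

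The count of 25 splits the listed items: 2 muscles + 1 balance + 3 spirometry + 2 respiratory pressures + 1 peak flow + 3 tape levels + 1 thermography + 1 heart rate variability + 1 lactate + 1 walk test + 8 quality-of-life domains + 1 cognition = 25.

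**Step 3. If all 12 measures were also tested at all three post-baseline visits.** This is one possible reading, not a documented plan. Assumed between-visit correlation 0.7:

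| Chance of at least one of the following | ρ = 0.3 | ρ = 0.5 | ρ = 0.7 |
|---|---|---|---|
| CR-PBM vs CR-PlaceboPBM, P < .05 in either direction | 68% | 58% | 45% |
| The same contrast, favouring PBM only | 37% | 30% | 22% |
| Three-group omnibus test, P < .05 | 69% | 58% | 46% |
| Both contrasts with CR-PBM, P < .05 in either direction | 88% | 80% | 66% |

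For results favouring PBM only, the nominal rate for a single test is 2.5%.

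**Step 4. What one primary test would give.** Type I error is 5% two-sided. The difference detectable with 80% power, by the normal approximation, is (1.960 + 0.842) × √(2/30) = 0.72 SD. A two-sample t-test with 30 per group needs about 0.74 SD. If all 12 measures were kept as co-primary at one visit and one contrast under Bonferroni, the threshold would be 0.05/12 = 0.0042 and the normal approximation gives (2.865 + 0.842) × √(2/30) = 0.96 SD.

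**The case against.** The strongest objection is that section 2.9 states a threshold and little else. It fixes no test, no pairwise comparisons and no visit-by-visit testing, and it does not exclude omnibus or repeated-measures analyses. Choice of test and adjustment for multiplicity are commonly left to an analysis plan, and this is a condensed article. That much stands: the absence of a multiplicity method is not itself the point, and the absence of a primary outcome is established only for the text shown. But choosing the primary outcome is a protocol-level decision, and the article does give a full outcome list and a significance rule without making it. An omnibus test in place of pairwise tests would not solve the problem either, as Step 3 shows.

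A reader might infer that a false PBM claim is close to certain, by multiplying 12 measures × 3 pairs × 3 visits = 108 tests. The documents do not support that:

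- The full set of tests is an inference.
- Of the 108, 12 × 3 = 36 compare CCR with CR-PlaceboPBM and cannot yield a PBM claim.
- Two-sided counts include results against PBM.
- The article does not say that all 12 measures are taken at every visit. Heart rate variability and lactate are tied to treadmill training, and no training session is described at the two-month follow-up.

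It would also go too far to say that the trial cannot test its hypothesis. The lack of a hierarchy weakens the inference but does not rule it out.

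**Conclusion.** The point holds. In the text shown, no primary outcome, time point or contrast is named among 12 unranked measures, and one unadjusted threshold governs them all. On the narrow reading (CR-PBM versus CR-PlaceboPBM at a single visit) the chance of at least one false positive is 46% under independence and about 23% to 40% at assumed correlations of 0.7 to 0.3. That is roughly five to nine times the nominal 5%. Testing more visits, contrasts or sub-measures raises it. The exact rate cannot be stated, because the set of tests is not fixed and every correlation is an assumption, but it was well above the nominal level in every scenario computed.

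**What to change.** Before unblinding, name one primary variable, one visit and one contrast in sections 2.8 and 2.9. One choice that fits the stated hypothesis is a defined exercise-tolerance variable from the adapted 6-minute walk test at week 9, CR-PBM versus CR-PlaceboPBM, at two-sided 0.05. Naming the walk test alone is not enough: section 2.8 describes it as exercise-tolerance parameters together with vital-sign responses, so the single variable must be specified. If a fuller protocol or analysis plan already names a primary outcome, carry it into these sections.

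Make all other outcomes, visits and contrasts, and all within-group tests, secondary. Either adjust them by Holm within one named family, or report estimates with 95% confidence intervals and make no efficacy claim from them.

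The cost is wording; no extra patients or procedures are needed. The downside is that secondary results can no longer be claimed as significant at an unadjusted 0.05, and that the single primary test with 30 per group has 80% power only for a difference of about 0.74 SD.

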## Discussion

3

New therapies are evolving to improve quality of life for patients affected by diseases of the central nervous system, and there has been a focus on physical conditioning to enable improvement in social activities and activities of daily living. Individuals with neurological impairment have decreased cardiorespiratory fitness, generally perform insufficient recommended physical activity, either through sedentary sequelae or habit.^[12]^ Sedentary individuals are at a higher risk of death and are twice as likely to suffer from cardiovascular disease, compared with physically active persons.^[27]^

Residual motor limitation, as a result of neurological impairment, causes difficulty in muscle recruitment, altered muscle tone, decreased resistance, and high energy expenditure. A sedentary lifestyle also promotes changes in the autonomic system, which directly impacts cardiac tissue functionality, and leads to negative peripheral cardiovascular adaptations, such as reduction of artery diameter and increased vascular resistance. Aerobic training, in addition to potentiating functional recovery, stimulates a neuroprotective effect in the brain, acting on cortical and subcortical regions.^[11–29]^

Aerobic exercise is a part of cardiovascular rehabilitation in these patients, where the main objectives are to reduce cardiovascular risks and to rehabilitate the patient in an integral way, offering support in physical, psychological, social, vocational, and spiritual aspects of quality of life^[26]^ Saunders et al ^[30]^ argue that there is a strong argument that cardiorespiratory training involving walking should be inserted into post-stroke rehabilitation programs, as it stimulates function, cadence, and gait tolerance. Moreover, economic evaluation analysis shows that the effectiveness of cardiovascular rehabilitation brings clinical benefits (years of life earned). When this is divided by the monetary value (cost), this manifests in a reduction in the cost of each additional year of life, in comparison with alternative treatments or absence of treatment.

According to Coote et al,^[16]^ the scarcity of studies investigating medium- and long-term benefits of aerobic training and resistance interventions in individuals with multiple sclerosis is of concern. However, a minimum of 30 minutes of moderate-intensity aerobic exercise and resistance training twice a week is recommended, based on area guidelines. In order to promote positive cardiovascular adaptations and improved respiratory capacity, Van der Scheer et al^[31]^ report that adult individuals with spinal cord injury should perform at least 20 minutes of vigorous intensity aerobic activity and 2-fold strength training exercises per week. Chin et al^[32]^ carried out a 12-week supervised aerobic training program in patients with traumatic brain injury and demonstrated improvements in cardiorespiratory fitness and fatigability. Their study highlighted the importance of performing exercise at the correct intensity for each individual. PBM Therapy, formerly known as low-level laser therapy, is able to trigger a range of physiological effects, through increased cellular metabolic energy production and reduced oxidative stress. These effects occur due to the increased activation of cytochrome C oxidase (the terminal enzyme of the electron transport chain) through light absorption, leading to improved oxygen consumption, cerebral blood flow, and neuronal metabolic capacity.^[33]^

A number of PBM Therapy research studies have investigated attention, memory, anxiety and depression, as well as increased cortical oxygenation. The literature describes PBM Therapy as a safe, noninvasive treatment, with no reported side effects.^[33,34]^

We hypothesize that exposure of neural tissue to PBM Therapy could, through vasodilation and increased cerebral perfusion, also lead to positive effects peripherally. Therefore, we propose that combining the effects of aerobic exercise and PBM Therapy will increase performance in physical activity in patients affected by diseases of the central nervous system.
